## Abstract

**Background:**

Tennis elbow is a common elbow pathology typically affecting middle-aged individuals that can lead to significant disability. Most cases resolve within 2 years of symptom onset, but a subset of patients will develop persistent symptoms despite appropriate conservative management. There are several surgical approaches used to treat chronic tennis elbow, with arthroscopic surgery becoming an increasingly popular approach to address this pathology in North America. This procedure involves the arthroscopic release of the extensor carpi radialis brevis tendon (ECRB) origin at the elbow. The potential benefit of arthroscopic treatment of this condition is improved patient outcomes and shorter recovery time following surgery. The results of this technique have been reported only in the context of case series, which have shown positive results. However, in order to justify its widespread use and growing popularity, a high level of evidence study is required. The purpose of this prospective, randomized sham-controlled trial is to determine whether arthroscopic tennis elbow release is effective at treating chronic lateral epicondylitis.

**Methods:**

We will conduct a prospective single center, double-blind, randomized sham-controlled parallel arm trial evaluating the efficacy of arthroscopic tennis elbow release in adult patients with symptoms for at least 6 months. Patients will undergo intraoperative randomization after diagnostic arthroscopy of the elbow to receive either ECRB release (through the creation of a lateral portal) or a sham lateral portal and no ECRB release. The primary outcome will be the Mayo Elbow Performance Score (MEPS) at 1 year follow-up. Secondary outcomes will be the abbreviated Disability of the Shoulder and Hand (DASH) score, American Shoulder and Elbow Surgeons elbow (ASES-e) score and grip strength at 3, 6, 12 and 24 months as well as return-to-work time, ability to return to full duty and adverse outcomes.

**Discussion:**

Results of this study will provide empirical high quality evidence to guide clinical decision-making in patients with chronic tennis elbow.

**Trial registration:**

NCT02236689 (September 8, 2014)

## Background

Lateral epicondylitis (tennis elbow) is a common occurrence in the general population with an incidence of 4-7/1000/year [1–3]. More recent literature describes a 1–3 % rate over the course of a lifetime, most typically affecting individuals between the ages of 35 and 50 [4]. Despite its name, this condition affects a wide variety of individuals, including politicians, municipal utility employees, cooks, meat industry employees as well as nonlabor workers. One study looking at the financial burden of elbow epicondylitis in Washington State from 1987 to 1995 found that it accounted for 11.7 % of work-related injury claims, costing $6,593 per case in average direct workers’ compensation [5].

Although tennis elbow can present acutely, the onset is often insidious secondary to repetitive wrist extension and alternating forearm pro-supination. Symptoms include lateral elbow pain and forearm weakness that is exacerbated by repetitive extension and/or rotation of the wrist. Grip strength is also typically diminished. Its natural history is often reported as 6–24 months, [6–8] with more than 80 % of cases achieving complete resolution at 1 year [9–11]. However, some studies report a full recovery rate as low as 34 % by 12 months [12].

Non-operative treatment consists mainly of activity modification, nonsteroidal antiinflammatory medications, physical therapy, counterforce bracing and corticosteroid injection [13]. Many authors recommend at least 6 months of non-operative management before considering operative intervention [14, 15]. Despite these measures, some patients will develop chronic symptoms refractory to conservative care.

Surgical indications for the management of lateral epicondylitis include persistent pain and failed adequate conservative management. The goals of surgery are to directly address that area of pathology through a procedure that involves resection of the involved tissue, to stimulate neovascularization and to produce a healthy scar while doing the least possible damage to surrounding tissues [16]. Current surgical options can be classified into open, percutaneous and arthroscopic, with arthroscopic tennis elbow release (ATER) having gained popularity over the past fifteen years with improved understanding of three-dimensional elbow anatomy and advances in arthroscopic procedures and equipment. When performed by experienced specialists, arthroscopic surgery allows for the assessment and debridement of concomitant intra-articular pathology such as synovitis, radiocapitellar plicae, osteochondral defects and intra-articular loose bodies that are often missed and can be a frequent cause of residual pain following extensor carpi radialis brevis (ECRB) release [17–20]. For example, in a retrospective review of 36 patients treated arthroscopically for tennis elbow, 28 % had significant intra-articular synovitis requiring debridement [21]. The rehabilitation process and time back to work following arthroscopic treatment is faster in comparison to the other surgical approaches and the outcomes are generally reported as equal or better [17, 19, 22, 23]. A recent retrospective cohort study on 341 consecutive patients comparing arthroscopic to open release demonstrated significant differences in Disability of the Shoulder and Hand (DASH) scores and total number of excellent outcomes between groups, favoring arthroscopy [24].

Despite the increased popularity of ATER in recent years, there have been no randomized-controlled trials evaluating its efficacy. A recent systematic review concluded that there is fair-quality evidence for elbow arthroscopy in the treatment of lateral epicondylitis (grade B recommendation) on the basis that outcomes appear to be similar to open surgery [25]. This recommendation is based on two cohort studies (Level III) and eight case series (Level IV) all reporting good to excellent results for arthroscopic surgery. However, a subsequent Cochrane review concluded that due to the small number of studies, large heterogeneity in interventions across trials, small sample sizes and poor reporting of outcomes, there was insufficient evidence to support or refute the effectiveness of surgery for tennis elbow [26].

The arthroscopic approach to the treatment of lateral epicondylitis has been widely adopted in North America. However, no comparative studies have demonstrated its efficacy. In order to provide optimal care to patients and to justify the increased cost and utilization of resources required for this treatment, a high level of evidence study is essential. This study aims to elicit whether ATER is efficacious at treating chronic tennis elbow.

## Methods

### Study design

This study is designed as a prospective single center, double-blind, randomized sham-controlled parallel arm trial, stratified on the need for debridement. After diagnostic arthroscopy, patients will be randomly assigned to ATER or sham (i.e. placebo) surgery and stratified by whether they require debridement or not. The study is designed to abide by the current international research standards and will be reported according to the guidelines listed in the CONSORT statement [27]. The study is approved by the Ottawa Health Science Network Research Ethics Board of Ottawa, Canada and is in compliance with the Tri-Council Policy Statement: Ethical Conduct for Research Involving Humans; the International Conference on Harmonization – Good Clinical Practice: Consolidated Guideline and the provisions of the Personal Health Information Protection Act 2004.

The surgeries will be performed by a single fellowship-trained upper extremity orthopaedic surgeon with at least seven years of independent practice experience at a university-affiliated academic center.

### Purpose and hypothesis

The purpose of the study is to determine whether ATER is superior to non-operative management using a sham surgery control group for the management of chronic lateral epicondylitis of the elbow at 24 months postoperative as measured by the Mayo Elbow Performance Score (MEPS). Data will be collected at baseline and at 3, 6, 12 and 24 months following surgery. In addition, we will aim to determine if there is a differential effect of ATER versus sham surgery among the subgroup of patients requiring additional elbow debridement due to coexisting intra-articular pathology. Furthermore, we will compare the effect of ATER and sham surgery on the abbreviated DASH and American Shoulder and Elbow Surgeons Elbow (ASES-e) scores at the different timepoints, as well as assess for any differences in grip strength, return to work time and adverse outcomes between the two groups.

We hypothesize that at 24 months, the improvement in MEPS is greater after ATER than sham surgery. Furthermore, we hypothesize that the DASH, ASES-e will also favor ATER at all postoperative timepoints. In addition, we hypothesize that grip strength will be diminished in the ATER group compared to sham, but that return to work time will favor ATER Table 1.

**Table 1 Tab1:** Data collection timeline

Variable	Baseline^a^Preoperative	T = 2 weeks Postoperative	T = 6 weeks Postoperative	T = 3 months Postoperative	T = 6 months Postoperative	T = 1 year^b^Postoperative	T = 2 years Postoperative
*Patient demographics*							
Age (years)	X						
Sex (M/F)	X						
Duration of symptoms (months)	X						
Arm affected (L/R)	X						
Dominant arm (L/R)	X						
Height (cm)	X						
Weight (kg)	X						
Body-Mass Index (BMI)	X						
Occupation	X						
Smoker (Y/N)	X						
Diabetic (Y/N)	X						
*Outcome measure*							
MEPS^c^	X			X	X	X	X
*Quick*DASH	X			X	X	X	X
ASES-e	X			X	X	X	X
Grip strength (grip dynamometer)	X			X	X	X	X
Return to work (Y/N)				X	X	X	X
Complications		X	X	X	X	X	X

^a^Second clinical visit

^b^Primary endpoint

^c^Primary outcome measure

### Participants

Patients eligible for inclusion in the study will be aged >18 years and have had symptoms for at least 6 months and have subsequently failed a 3-month course of conservative management consisting of activity modification, anti-inflammatories, physiotherapy, corticosteroid and platelet-rich plasma injections. Patients with an alternative diagnosis that better explains their symptoms or those who have had significant prior elbow trauma or surgery are not eligible to be a part of the trial. Workplace Safety and Insurance Board (WSIB) patients (workplace injuries) are also excluded from the study. Patients must be able to speak English. General Practitioners in the Ottawa area will be sent a letter asking them to refer patients who meet the eligibility criteria listed above. Eligible patients will receive informed consent on the two treatment arms. Enrolled participants will undergo a functional outcome scores assessment (MEPS, abbreviated DASH, ASES-e, grip strength) at the second preoperative clinical visit, which will serve as a baseline for comparison. They will then be scheduled for surgery through the standard outpatient surgery program.

### Randomization

The patients will be brought to the operating room where they will undergo a regional block anesthetic. A diagnostic arthroscopic evaluation will then be performed through a medial portal. Following this, the surgeon will make a decision as to whether the elbow requires any debridement. The decision to debride is a clinical one and is influenced by the presence of an intra-articular pathology, such as extensive synovitis (inflammation), loose bodies and radiocapitellar plicae. Patients who are deemed to require intra-articular debridement will receive it at this point. This requires the creation of a lateral, working portal. Patients who do not require debridement will be randomized to ATER or sham. Similarly, patients who do require debridement will be randomized to ATER or sham.

A randomization sequence will be computer generated by an independent statistician. Consecutive patients will be randomized to receive ATER or Sham surgery in a 1:1 allocation ratio, with stratification by the need for debridement and randomly permuted block sizes from 2, 4, or 6. Central randomization will be accomplished by the use of online registration and verification of eligibility through the Data Management Services group at the Ottawa Hospital Research Institute Fig. 1.

**Fig. 1 Fig1:**
[figure not shown]
Study flowchart. Legend: two parallel randomization arms; ATER (*blue*) and sham procedure (*green*)

### ECRB release

The patient is positioned in the lateral position with the body supported using a beanbag and the arm over a right-angle arm support. They are padded and protected appropriately. The patient’s bed is tilted towards the surgeon approximately 15° to avoid any traction on the brachial plexus. The patient is then prepped and draped in the standard sterile fashion. Anatomic landmarks are identified and marked using a marking pen. All portal sites are determined and marked. The elbow is injected with 25 mL of normal saline to provide capsular distention and safer portal placement.

The anteromedial portal is established first. This is done with a blunt trocar. The arthroscope is then inserted into the elbow. The anterolateral portal is then established under direct visualization. This is also completed with a blunt switch stick. A 6 mm dilator is then placed over the switch stick.

Next, a shaver is used to remove the lateral capsule in order to visualize the ECRB. A wedge of the capsule in that region is removed. We are careful to avoid an anterolateral capsulectomy due to the proximity of the posterior interosseus nerve in this location. We are also careful during the procedure to avoid disrupting the ulnar lateral collateral ligament by staying anterior to the equator of the capitellum and radial head. Once the ECRB is visualized, a biting forceps is used to release the tendon. The extensor carpi radialis longus (ECRL) is left intact. Finally, a 1.5 × 1.5 × 1.5 triangular section of the ECRB tendon (and superior edge of the Extensor Digitorum Communis) origin is excised. The ECRL and LUCL are left intact. A complete release of ECRB is performed in order to obtain good visualization of the overlying ECRL.

After the release is completed, the elbow is examined to demonstrate full, smooth, concentric range of motion and to confirm that there is no evidence of catching or clicking. The elbow is examined with varus, valgus, rotational and axial stress to confirm that the LCL and MCL are intact.

### ATER: Intervention

Patients randomized to ATER will receive arthroscopic release of the origin of the ECRB tendon through a standard, two-portal arthroscopic technique.

### Sham surgery: Control

Patients randomized to sham surgery will not have the ECRB muscle origin released. Instead, they may receive a small incision only through the skin in the same position where a second lateral portal would otherwise be introduced, depending on whether or not they required elbow debridement in the prior step. If debridement was previously performed, the lateral portal will already have been created. If no debridement was required, they will receive a sham lateral portal, thus minimizing the risks associated with introducing a second true portal while also preserving the patient’s blinded status.

### Postoperative protocol

Post-operative follow-up is at 2 weeks, 6 weeks, 3, 6, 12 and 24 months. Functional outcome scores will be obtained from each patient at the 3, 6, 12 and 24 month time points. Post-operative management will be identical among the two treatment arms and consists of immediate elbow range of motion exercises and no weight-bearing restrictions. However, elbow, forearm and shoulder strengthening exercises will begin at 10 weeks postoperative. Patients (independent of concealed group allocation) will receive functional counseling by a licenced physiotherapist at the first postoperative visit and will be provided with a standardized exercise protocol to guide outpatient physiotherapy.

### Primary outcome

#### MEPS

All functional assessment forms will be administered electronically to patients by means of a touch-screen device at each follow-up appointment. Our primary outcome measure is elbow pain and function as measured by the MEPS at 24 months post-operative. The MEPS is a commonly used performance index for evaluation of clinical outcomes for a variety of elbow disorders that can be completely patient-administered [28]. It consists of four parts: pain, stability, ulnohumeral motion and the ability to perform five functional tasks. The highest possible score is 100, with scores 90 and above indicating excellent function [29].

### Secondary outcomes

#### DASH

The abbreviated (quick) DASH score is a self-reported questionnaire consisting of 11 items designed to measure symptoms and function in patients with upper extremity-specific pathologies. It is a shortened version of the DASH score, which normally consists of 30 items, and has been shown to retain its psychometric properties in a more user-friendly structure. At least 10 of the 11 items must be completed in order for the score to be valid. Each item is scored 1-5, with 1 indicating no difficulty and 5 indicating inability to perform the function questioned. The values are then summed up, averaged and converted to a score out of 100 by subtracting 1 and multiplying by 25. The higher the score, the greater the disability [30].

#### ASES-e

The ASES-e score is both patient and physician-administered. The patient-reported self-evaluation consists of pain, function and satisfaction components. The pain component utilizes the visual analogue scale (0 to 10, with 10 indicating the worst pain ever), while the function component pertains to the patient’s ability to perform specific upper extremity-related tasks (0 to 4, with 4 indicating no difficulty). Satisfaction is graded 0 to 10. The physician assessment consists of motion, strength (both in flexion, extension, pro-supination), stability (varus, valgus, posterolateral rotatory) and physical findings (tenderness, scars, etc). Stability is graded 0 to 3, with 3 grading gross instability, while strength is graded 0 to 5, with 5 indicating normal strength. Physical findings are reported as being present or not.

The MEPS, DASH and ASES-e scores are all validated, upper extremity-specific questionnaires [29]. We will also be testing grip strength using a standard grip dynamometer and compare return to work time and adverse outcomes between the two groups.

### Blinding

Patients will be blinded to treatment group through the use of a sham incision. Due to the nature of a surgical trial, the surgeon cannot be blinded to the intervention. However, a trained independent assessor, blinded to treatment status will conduct the follow-up examinations in a standardized fashion. This will minimize the potential for biases introduced by the examiner when performing the physical assessment and recording data. The assessor will not have access to the patient chart prior to the examination. To help reduce the potential for observer bias, the physical examination and the administration of study questionnaires are standardized.

### Control of contamination and co-intervention

There will be a possibility of cross-over after one year postoperative. This means that to remain a study participant, the patient may not learn which of the two groups they were randomized to until one year postoperative. However, should the patient be unsatisfied with their outcome prior to that mark, they may elect to withdraw themselves from the study and learn which treatment they received and pursue further treatment if appropriate.

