### Statistical considerations

#### Primary analysis

The primary analysis involves a comparison of the MEPS outcome measure between the two surgical treatment groups on an intention-to-treat basis at 24 months post-surgery as compared to baseline values. A two-sample independent ANCOVA will be used to assess whether there is a statistically significant difference between groups for the MEPS scores, accounting for the debridement stratification variable and baseline MEPS. Linear regression will be used to estimate treatment size effect, accounting for the stratification variable and baseline MEPS, as well as any possible imbalanced covariates. Primary analyses will be repeated for the debridement and no-debridement patient subgroups. Missing follow-up data will be addressed with multiple imputation techniques.

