#### Sample size calculation

The primary outcome is the modified Mayo Elbow Performance score. A minimum clinically importance difference of 15 points has been derived for patients with rheumatoid arthritis [31]. In a study of patients with elbow dysfunction, standard deviations ranged from 17 to 19 points [28]. In order to attain a study power of 80 % to detect a minimally clinically important difference of 15 points on the MEPS primary outcome measure at one year follow-up using ANOVA to compare ATER versus sham, and assuming a standard deviation of 19 points as well as an alpha level of 0.05, a total sample size of 52 patients will be required (group sizes of 26) [31, 32]. However, adjusting for the remote possibility of 5 % of patients requiring un-blinding in the case of sham surgery (drop out), and a possible 15 % loss to follow-up yields a total sample size of 68 (34 in each group).

Assuming a recruitment and consent rate of 70 %, we would need to approach 97 patients to achieve our required sample size. Hospital records indicate that our clinic sees approximately 10 eligible patients per month, meaning we can feasibly achieve our required sample size within 10 months of enrollment.

Patients who are excluded from the trial intra-operatively and patients whose symptoms resolve prior to intra-operative randomization will only be followed clinically and not as part of this study.

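### Patients who want their allocation before 1 year must leave the study, so outcomes are lost for a reason tied to the outcome itself

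*Protocol article*

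**What the plan says.** Four parts of the protocol article bear on this.

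- **Control of contamination and co-intervention** sets the rule: "to remain a study participant, the patient may not learn which of the two groups they were randomized to until one year postoperative". It then gives the exit for patients unhappy with their result before that point: "they may elect to withdraw themselves from the study and learn which treatment they received and pursue further treatment if appropriate".
- **Sample size calculation** inflates the target for this: "adjusting for the remote possibility of 5 % of patients requiring un-blinding in the case of sham surgery (drop out"), and separately for ordinary attrition: "a possible 15 % loss to follow-up yields a total sample size of 68 (34 in each group").
- **Primary analysis** compares MEPS between arms "on an intention-to-treat basis at 24 months post-surgery as compared to baseline values". On gaps in the data it says: "Missing follow-up data will be addressed with multiple imputation techniques".
- **Ensuring complete follow-up** lists general retention measures (contact details, a copy of the consent form, coordinator contact). None provides for assessing a patient who has asked to be unblinded.

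Table 1 schedules MEPS, QuickDASH and ASES-e at baseline and then at 3, 6, 12 and 24 months. The ASES-e section describes a satisfaction item graded 0 to 10.

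**The concern.** The exit is triggered by the thing the trial measures. A patient who is doing badly and wants to know why has one route to the answer before 1 year, and it runs out of the study. No part of the article keeps such a patient under assessment afterwards, so the later MEPS is missing because the result was poor. The article uses both 1 year and 24 months as the primary time point in different sections; a departure before 1 year loses the endpoint under either.

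Imputation that treats data as missing at random predicts the missing score from retained patients with the same recorded history. If dissatisfaction carries information beyond that history, the imputed scores are too high. The arms need not be affected equally. The article itself associates the unblinding with sham surgery, and its Discussion does not expect sham patients to benefit directly from their procedure. Unequal loss of failures biases the treatment difference, and scores that were never collected cannot be recovered by any later analysis plan.

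**Working it through.** **1. The plan's own figures.** Inputs from the sample size section: difference 15, SD 19, alpha 0.05 (two-sided assumed), power 80%.

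n per arm = 2 × (1.96 + 0.84)² × 19² / 15² ≈ 25.2, so 26 per arm and 52 in total, as stated. Normal-approximation power at 26 per arm is 81%. An exact t-test needs 26.18, so 27 per arm.

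Inflating for 5% + 15% = 20%: 26/0.80 = 32.5, so 33 per arm (66 in total); 27/0.80 = 33.75, so 34 per arm (68 in total). The stated 68 is reproduced from 27 and is within 2 patients from 26. The sample size is not at fault. The calculation confirms that unblinded patients are counted as lost.

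**2. What 5% means in patients.** Read as 5% of the sham arm: 0.05 × 34 = 1.7 patients. Read as 5% of all patients, all of them sham: 0.05 × 68 = 3.4 patients, and 3.4/34 = 10% of that arm.

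**3. Shift in the treatment difference.** Let p be the share of an arm that withdraws dissatisfied, and g the average excess of the imputed over the true score in those patients. Then

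shift in (ATER − sham) = −(p_sham − p_ATER) × g.

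The documents give no value for g; 10 to 30 MEPS points is an assumption. Power is by normal approximation at 26 per arm, for a true difference of 15.

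| Sham withdrawn | ATER withdrawn | Shift for g = 10 to 30 | Power |
|---|---|---|---|
| 5% | 0% | −0.5 to −1.5 | 79% to 73% |
| 10% | 0% | −1.0 to −3.0 | 76% to 62% |
| 10% | 10% | 0 | 81% |
| 20% | 5% | −1.5 to −4.5 | 73% to 51% |

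The first two rows are the two readings of the protocol's 5%. The last row is a what-if; no section gives those rates. Exchanging the arms reverses the sign.

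**4. How much earlier scores help.** A simulation used 34 per arm, a true difference of 15, SD 19 and correlation 0.3 to 0.7 between scores. Withdrawal was 8–22% in sham and 2–7% in ATER. Regression imputation stood in for multiple imputation, and scores were not capped at 100.

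- Withdrawal driven only by the recorded 6-month score: the estimate is about 15 with that score in the imputation model, and 14.0 to 14.7 without it.
- Withdrawal driven by the final outcome itself: the estimate is 11.4 to 14.2, with or without the 6-month score.

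So good use of earlier scores can remove the bias in the first case and barely touches it in the second. A patient who leaves before 3 months has no postoperative score to use.

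**5. Patients needed if follow-up continues.** Only the 15% loss then needs inflation: 26/0.85 = 30.6, so 31 per arm (62 in total); or 27/0.85 = 31.8, so 32 per arm (64 in total). Both lie within the planned 68, before any dilution by later treatment.

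**The case against.** A reader might infer that the withdrawal rule contradicts the intention-to-treat analysis. The documents do not support that. Multiple imputation keeps every randomised patient in the assigned arm, so the analysis set is intact; what is lost is observation of the endpoint. That these patients will be imputed is itself an inference from three sections read together, although no other handling is stated.

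A reader might also infer a bias of 20–40% of the target difference (3 to 6 points). The upper part of that range needs 15–20% of an arm to leave dissatisfied and gaps of 20 to 30 points. The article calls the possibility remote and puts it at 5%; its 15% is ordinary loss to follow-up, counted separately.

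Other points on that side stand in part:

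- MEPS, QuickDASH and the ASES-e satisfaction item are due at 3 and 6 months. For patients who leave after those visits they could make missing-at-random plausible. This does not help earlier leavers, or those whose decline came after the last recorded visit.
- The imputation model and any sensitivity analysis may properly sit in an analysis plan that is not shown. Their absence is not part of this point, which rests on the withdrawal rule.
- If losses are mainly sham, the bias runs against ATER: it costs power and does not create a false benefit. The direction rests on the protocol's expectation, which may prove wrong.
- Scores obtained after unblinding or further treatment have their own problem. MEPS is patient-completed, and a sham patient who improves on later treatment also raises the sham mean. Whether such scores belong in the main comparison depends on the treatment effect being targeted.

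**Conclusion.** The point holds in a limited form. The rule makes leaving the study the price of learning the allocation before 1 year. Outcomes are therefore lost for a reason related to the outcome, and the comparison rests on modelled endpoints for some likely failures. At the protocol's own 5% the shift is about 0.5 to 1.5 MEPS points, or 1 to 3 if the 5% refers to all patients and all are sham. That is 3–10%, or 7–20%, of the 15-point target. These figures rest on the assumed 10 to 30 point gap and on no dissatisfied withdrawals in the other arm; equal losses and equal gaps would cancel. The effect exceeds this range only if dissatisfaction is commoner than planned or the gap is wider. Confidence is high that the rule operates this way and low on the size of the bias. It deserves moderate priority: the expected effect is modest, but the loss is irreversible and cheap to prevent. It does not by itself invalidate the trial.

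**What to change.** - Reword the section on contamination and co-intervention, and the consent form, so that a request for unblinding ends blinding but not study follow-up.
- Record MEPS, QuickDASH and ASES-e when the request is made, before the allocation is disclosed.
- Continue the scheduled assessments for patients who agree, flag every score obtained after unblinding or further treatment, and keep these patients in their randomised arm.
- Keep the pre-disclosure score available for a supporting analysis.

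Patients retain the same right to unblinding, to further care and to full withdrawal; only data collection changes.

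The cost is an edit to the protocol and consent wording and one additional set of scores per request. No extra patients are needed on the document's own inputs. The real downside is that scores after unblinding or further treatment are open to expectation and may dilute the contrast, which is why the flag and the pre-disclosure score are needed.
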